## Abstract

**Introduction::**

Allergic rhinitis (AR) is an immunoglobulin E (Ig E)-mediated inflammatory disease. Intranasal phototherapy is a promising treatment modality because it has a profound immunosuppressive effect, but the evidence of its use for AR is insufficient. Therefore, rigorously designed randomized controlled trials (RCTs) are needed. Our objective is to describe the protocol for an RCT to assess the effects and safety of intranasal phototherapy for the treatment of AR.

**Methods and analysis::**

This is a study protocol for a single-center, randomized, parallel (acupuncture-controlled), open-label, investigator-initiated, pilot study. A total of 80 patients with AR will be randomly assigned to the intranasal phototherapy or acupuncture group at a 1:1 ratio. The participants will receive intranasal phototherapy with medical or acupuncture treatment for 20 minutes, 3 times a week for 4 weeks. The primary outcome will be the mean change in the total nasal symptom score (TNSS) from baseline to 4 weeks. The secondary outcomes will include the Rhinoconjunctivitis Quality of Life Questionnaire (RQLQ) score, Nasal Endoscopy Index, total serum immunoglobulin E (Ig E) level and eosinophil count.

**Discussion::**

The findings of this study will provide the basis for the design and implementation of RCTs investigating the effects and safety of intranasal phototherapy for AR. Additionally, it will provide preliminary evidence of intranasal phototherapy for use in AR.

**Trial registration::**

This study was registered at the Korean National Clinical Trial Registry, Clinical Research Information Service (KCT0004079).

## Introduction

1

Allergic rhinitis (AR) is an inflammatory disease of the nasal membranes that results from an IgE-mediated immune reaction to allergen exposure.^[1]^ The major symptoms of AR are nasal congestion, rhinorrhea, nasal itching and sneezing, and it is reported that patients with AR often have poor quality of life (QOL). Moreover, AR disrupts sleeping, interrupts learning and reduces productivity at work.^[2]^

AR is a common respiratory disease that affects 10% to 25% of the global population,^[3]^ and it affects 22% to 29.2% of the pediatric population and 20% of the adolescent population in Korea.^[4]^ It has been reported that the prevalence of persistent allergic rhinitis (PAR) has increased over the last decade.^[5]^

The management of AR involves allergen avoidance and medication such as antihistamines and nasal decongestants.^[6]^ Antihistamines relieve the symptoms of AR, but symptom relief may be incomplete,^[7]^ and long-term use of nasal decongestants can cause rhinitis medicamentosa.^[8]^ Additionally, there are some patients whose symptoms do not improve completely even with these medications and who have some limitations and special considerations in terms of using these medications, such as patients who are pregnant or breastfeeding.^[9]^

Low-level laser therapy (LLLT) is a promising treatment modality in Korean medical fields, and intranasal phototherapy represents an alternative intervention in the treatment of AR.^[10,11]^ Intranasal phototherapy is the application of light into the nasal cavity to relieve the symptoms of AR by inducing apoptosis of immune cells to suppress the reaction of inflammatory mediators^[12]^ and is expected to relieve the symptoms of AR for patients who do not respond well to conventional therapy.^[13]^ However, further studies are required on this topic to draw reliable conclusions about the effects and safety.^[14]^

We designed a single-center, randomized, parallel, open-label, investigator-initiated, pilot study to validate the clinical effects and safety of intranasal phototherapy for AR compared to those of acupuncture treatment, which is used as a usual care. The results of this study are expected to provide preliminary evidence of intranasal phototherapy for use in AR.

## Methods

2

### Objective

2.1

The aim of this study is to describe the protocol for a randomized controlled trial designed to clinically assess the effects and safety of intranasal phototherapy for AR compared with acupuncture treatment.

### Study design and setting

2.2

This is a single-center, randomized, parallel (acupuncture-controlled), open-label, investigator-initiated, pilot study. This study will be conducted at the Woosuk University Korean Medicine Hospital, Jeonju, Republic of Korea.

A total of 80 participants will be recruited for this trial and will be randomly allocated to 2 parallel groups: the intranasal phototherapy group or the acupuncture group. According to their group allocations, the participants will receive intranasal phototherapy or acupuncture treatment. The total study period will include a 4-week intervention and a 4-week follow-up. The study design is summarized in Fig. 1 and Table 1. The study protocol (version 1.1) was developed as required by the Standard Protocol Items: Recommendations for Interventional Trials (SPIRIT) guidelines (Additional file 1).

**Figure 1 F1:**
[figure not shown]
Flowchart of this study.

**Table 1 T1:**
[figure not shown]
Study design schedule.

### Recruitment

2.3

The recruitment posters will be displayed on the hospital bulletin board. The posters will contain brief descriptions and outline the purpose of this study, the inclusion criteria, and the intervention. A total of 80 participants will be recruited, and written informed consent will be obtained from all study participants before enrollment. All participants will have the right to participate or withdraw from the study at any time without penalty.

### Participant inclusion and exclusion criteria

2.4

#### Inclusion criteria

2.4.1

Participants will be included in this study if they meet all of the following criteria:

1.aged ≥19 years2.presence of 2 or more symptoms of allergic rhinitis (nasal congestion, rhinorrhea, nasal itching and sneezing) and3.positive reaction to an allergen in a multiple allergen simultaneous test (MAST).

#### Exclusion criteria

2.4.2

Participants will be excluded if they meet any of the following conditions:

1.Currently taking any of the following medications or cannot stop taking medication that is unsuitable for this clinical trial. (However, enrollment in this trial is possible after the suggested minimum wash-out period before Visit2.)Use of antihistamines/H1 blockers within the previous weekUse of corticosteroids (intranasal) within the previous 2 weeksUse of corticosteroids (systemic) within the previous 30 daysUse of anticholinergic drugs within the previous weekUse of leukotriene receptor antagonists within the previous 4 weeksUse of decongestants within the previous 3 daysUse of tricyclic antidepressants or phenothiazines within the previous 2 weeksUse of nonsteroidal analgesics within the previous 2 weeksOthers (inappropriate medications judged by the investigator)2.Received traditional Korean medicine treatments (herbal medicine, acupuncture, moxibustion, cupping, etc.) to treat allergic rhinitis within the previous 2 weeks3.Received laser therapy to treat allergic rhinitis within the previous 2 weeks4.Received treatments due to acute upper respiratory infections or sinusitis within the previous 4 weeks5.Has nonallergic rhinitis such as vasomotor, infectious, drug-induced rhinitis, or other severe nasal illness6.Has anatomical obstructions or deformities of the nasal cavity or underwent nasal surgery within the previous 6 months7.Diagnosed with malignant neoplasm, anemia, active pulmonary tuberculosis, infection, or other severe systemic disease8.Has a past history of active respiratory diseases such as asthma9.Received immunotherapy or systemic corticosteroid therapy within the previous 5 years10.Has hypersensitivity reactions to phototherapy or from taking related drugs11.Has a scar on the irradiation (or acupuncture) spot12.Are pregnant, planning a pregnancy or breastfeeding13.Participated in other clinical trials within the previous 1 month14.Has difficulties enrolling in this trial or receiving treatment15.Others: ineligible for participation as judged by the investigator

### Intervention

2.5

Subjects will be randomly assigned to 2 groups: an experimental group (medical device that emits low-level laser light) or a control group (acupuncture) at a ratio of 1:1. The experimental group will receive phototherapy in a single nasal cavity for 20 minutes, 3 times a week for 4 weeks. At each visit, the investigator decides on which side to receive phototherapy (right or left) based on the subjects symptoms and nasal endoscopy images. The medical device that will be used is the COBISTOP-S unit (Cngmedical Co., Ltd., Ulsan, Republic of Korea), which emits a low-level laser light consisting of a wavelength of 650 nm. The control group will receive acupuncture treatment for 20 minutes, 3 times a week for 4 weeks. Acupuncture will be performed by qualified Korean medicine doctors with at least 2 years of clinical experience. Ten acupuncture points (bilateral LI4, LI20, ST2 and ST36 and unilateral EX-1 and GV23) according to the “WHO Standard Acupuncture Point Location”^[15]^ were selected based on existing papers,^[16]^ and a 0.20 mm (diameter) × 30 mm (length) disposable needle (Dongbang Medical Co., Boryung-si, Republic of Korea) will be used. To induce de-Qi sensation, the needles will be manually manipulated 2 times, immediately after needling and before withdrawing. Acupuncture treatment details such as the acupuncture rationale, needling details, treatment regimen, cointervention, and practitioner background will conform to the Standards for Reporting Interventions in Controlled Trials of Acupuncture (STRICTA) checklist in Table 2.^[17]^

**Table 2 T2:**
[figure not shown]
Details of acupuncture treatments for allergic rhinitis, based on the STRICTA 2010 checklist.

### Outcome measures

2.6

#### Primary outcome

2.6.1

The primary outcome is the change in the total nasal symptom score (TNSS) from baseline to 4 weeks. The TNSS assesses 4 nasal symptoms (nasal congestion, rhinorrhea, nasal itching and sneezing) on a five-point scale: 0, no symptoms; 1, mild; 2, moderate; 3, severe; and 4, very severe.^[18]^ The TNSS will be measured at every visit, and we will analyze the differences in effects between the 2 groups.

#### Secondary outcomes

2.6.2

The secondary outcomes will include the change in the Rhinoconjunctivitis Quality of Life Questionnaire (RQLQ) score, Nasal Endoscopy Index, total serum immunoglobulin E (IgE) level, eosinophil count level, and adverse events. The RQLQ is a rhinoconjunctivitis-related quality of life instrument consisting of 28 items in 7 domains (activity limitation, sleep problems, nose symptoms, eye symptoms, non-nose/eye symptoms, practical problems and emotional function).^[19,20]^ The RQLQ score will be assessed 4 times: just prior to the start of the treatment, at visit 2 and visit 8, and at the 2 follow-up periods.

The Nasal Endoscopy Index assesses nasal cavity conditions according to 4 aspects: color (pale or hyperemia), dryness or dampness, rhinorrhea, and atrophy or edema.^[21]^ The Nasal Endoscopy Index will be evaluated at every visit. The instrument used will be the KAZAMA ENT treatment unit (KAU-3000 HARMONY, ENT Co., Ltd., Incheon, Republic of Korea).

We will also examine the total serum IgE level and eosinophil count at screening (visit 1) and visit 14 to evaluate the effects of intranasal phototherapy on allergy and inflammatory reactions.

#### Other measures

2.6.3

To identify the correlation between the effects of the interventions and the cold-heat pattern, we will use the Cold-Heat Pattern Identification Questionnaire. The questionnaire consists of 15 items, which include 8 items related to cold and 7 items related to heat,^[22]^ and the questionnaire will be assessed at screening.

### Randomization and allocation concealment

2.7

Participants who meet all the inclusion and exclusion criteria will receive a subject identification code. Accordingly, block randomization will be performed to assign the same number of subjects to the intranasal phototherapy or acupuncture group. A total of 80 participants will be randomly assigned to each group with a 1:1 ratio. A statistician who is not directly involved in this trial will generate a random allocation sequence using a computer program [Strategic Applications Software (SAS), version 9.3; SAS Institute Inc., Cary, NC]. The allocation for each randomization number will be put into individually sealed, consecutively numbered security envelopes. Consent will be obtained by a Korean medicine doctor, and before the random assignment, all participants will be informed that they will be assigned to 1 of 2 groups. After the participants have signed the informed consent form, the envelopes will be opened.

### Blinding

2.8

The investigator performing the outcome assessments will be blinded to the group allocation data. However, the subjects and the investigators who perform the intervention will not be blinded due to the characteristics of the study. The subjects will receive intranasal phototherapy or acupuncture treatment according to their randomization number.

### Sample size

2.9

Since the aim of this study is to determine preliminary feasibility, there will be no sample size calculation. We will conduct a pilot study with a sample size of 80 participants (40 in the intranasal phototherapy group and 40 in the acupuncture group) based on the previous pilot study,^[23]^ and we predict that the drop-out rate will be 20%. A total of 64 patients are predicted to complete the study. This sample size is considered to be sufficient to provide power analysis and sample size calculation for subsequent large-scale definitive RCTs.

### Data management

2.10

The investigators will telephone the participants before every visit to promote participant adherence. If participants fail to attend treatment sessions, we will ask the reasons for the absence and encourage visits through telephone contact.

Regular monitoring will be conducted to control the quality of the data according to the planned protocol and standard operating procedures. Medipert, the clinical research organization (CRO) of this study, will send a clinical research associate (CRA) to Woosuk Korean Medicine Medical Center. The CRA will check whether the trial is conducted according to the approved protocol and whether the data are adequately recorded. Each participants contact or identifying information will be separately stored. Personal identity will not be disclosed. Additionally, investigators will not collect any other personal data. All data and records related to the clinical trials should be kept in a locked cabinet. Documents related to this clinical trial will be kept for 3 years after completion of the clinical trial.

### Safety and adverse events

2.11

The participants will be educated to voluntarily report information about adverse events (AEs), and the investigator will check any expected or unexpected AEs. AEs such as nasal dryness, nasal septum perforation, burning, epistaxis (nosebleed), inflammation or stinging, or other AEs reported during the study period will be recorded in case report forms, and participant vital signs will be checked at every visit. The symptoms, date of occurrence and disappearance, severity, causal relationship with the treatment, other medications or treatments suspected to have caused the AE, and treatment for the AE will be recorded in detail. When serious AEs occur, the investigator will immediately report the event to the institutional review board (IRB) and decide whether to cease the treatment. Additionally, AEs associated with the intervention during the trial will be appropriately handled, and we will provide corresponding compensation according to insurance policy.

### Statistical analysis

2.12

The statistical analysis, including of the primary and secondary outcomes, will be performed using the full analysis set based on the principle of intention-to-treat (ITT); the per-protocol (PP) analysis set will be used for the sensitivity analysis. We will apply the last-observation-carried-forward (LOCF) rule for missing data.

Baseline differences between groups will be assessed using an independent two-sample *t* test or the Wilcoxon rank-sum test for continuous variables and the Chi-Squared test or Fisher exact test for categorical variables. Paired *t* test or Wilcoxon signed-rank test will be performed to analyze differences in the primary and secondary outcomes before and after treatment in each group. To demonstrate noninferiority, we will check whether the upper limit of the one-sided 97.5% confidence interval (CI) of the difference in the primary outcome between the 2 groups is less than the noninferiority margin (2 points).^[16]^ A subgroup analysis will also be performed to explore differences in the effects of intranasal phototherapy or acupuncture treatment according to the cold-heat pattern, symptom severity, and so on.

All participants who received at least 1 session will undergo an adverse effect evaluation. All adverse effects reported during the clinical trial will be analyzed. To compare groups and the incidence frequency of adverse events related to the 2 groups, the Chi-Squared test or Fisher exact test will be used. The level of significance will be set at 0.05 (2-tailed), except for the primary outcome, and all analyses will be performed using SAS version 9.3 (SAS Institute. Inc., Cary, NC).

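### As written, the noninferiority interval is a difference in TNSS change with no baseline covariate named; adjusting for baseline TNSS would narrow it at no cost

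*Protocol article*

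**What the plan says.** Protocol article, section 2.6.1 (Primary outcome): "The primary outcome is the change in the total nasal symptom score (TNSS) from baseline to 4 weeks". The score sums four symptoms rated 0 to 4, so it runs from 0 to 16 and higher is worse. It is measured at every visit.

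Section 2.12 (Statistical analysis): the decision rests on an upper one-sided 97.5% limit, with this rule: "confidence interval (CI) of the difference in the primary outcome between the 2 groups is less than the noninferiority margin (2 points". No model or covariate is named for this interval.

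Baseline enters section 2.12 in three other ways:
- Significance tests between arms: "Baseline differences between groups will be assessed using an independent two-sample" t test or its rank counterpart, with categorical tests alongside.
- Within-arm paired tests, which "will be performed to analyze differences in the primary and secondary outcomes before and after treatment in each group".
- An exploratory subgroup analysis that includes symptom severity.

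Section 2.7 (Randomization and allocation concealment): "block randomization will be performed to assign the same number of subjects to the intranasal phototherapy or acupuncture group". The stated purpose is equal numbers; the article mentions no stratification by baseline score.

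Section 2.9 (Sample size): 80 participants, 40 per arm, no sample size calculation, 20% predicted dropout and 64 predicted completers.

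**The concern.** A change score subtracts the whole of each patient's baseline value. Unless week-4 TNSS rises one for one with baseline, that over-corrects: an arm that starts higher by chance will on average fall further, through regression to the mean alone. Part of the chance imbalance then stays in the treatment difference, and the extra noise widens the interval. Regression on baseline TNSS removes the right amount.

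The decision depends on where one confidence limit falls relative to 2 points, in a trial of at most 80 patients, so both the width and the centre of the interval matter. The significance tests at baseline do not help: under randomisation any difference they detect is due to chance, and the primary estimate is unchanged whatever they show.

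**Working it through.** **The plan's own figure.** 80 × (1 − 0.20) = 64 completers, or 32 per arm. This reproduces. No power or SD-based figure is stated, so there is nothing further to reproduce.

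**Inputs from the article.** Change in TNSS as outcome (2.6.1); one-sided 97.5% limit and 2-point margin (2.12); 1:1 allocation (2.7); 40 randomised and 32 predicted completers per arm (2.9).

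**Inputs assumed.** The correlation rho between baseline and week-4 TNSS, equal SD s at both times, and the size of that SD. The article gives none of these, so ranges are shown.

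**Step 1: relative precision.** Per-patient variance:
- change score: 2s²(1 − rho)
- ANCOVA on baseline: s²(1 − rho²)
- ratio, ANCOVA to change score: (1 + rho)/2
- extra patients needed by the change score: 2/(1 + rho) − 1

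| rho (assumed) | Variance ratio | SE reduction, 1 − √ratio | Extra patients |
|---|---|---|---|
| 0.3 | 0.65 | 19% | 53.8% |
| 0.5 | 0.75 | 13% | 33.3% |
| 0.7 | 0.85 | 8% | 17.6% |
| 0.8 | 0.90 | 5% | 11.1% |
| 0.9 | 0.95 | 3% | 5.3% |

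Allowing for one estimated covariate at N = 64, the figures for rho 0.3, 0.5 and 0.7 become about 51%, 31% and 16%.

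If the SDs differ (s0 at baseline, s1 at week 4), the change-score variance exceeds the ANCOVA variance by s0² + s1² − 2·rho·s0·s1 − s1²(1 − rho²) = (s0 − rho·s1)². This is never negative, so the direction of the result does not depend on equal SDs; only its size does.

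**Step 2: interval half-width.** Half-width = t(0.975) × SD of change × √(2/n). ANCOVA multiplies it by √0.75 = 0.866 at rho 0.5.
- 32 per arm, SD of change 3: 2.00 × 3 × √(2/32) = 1.50; × 0.866 = 1.30.
- 40 per arm, SD of change 3: 1.99 × 3 × √(2/40) = 1.34; × 0.866 = 1.16.

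Half-width is proportional to the SD. With 32 per arm it falls from 1.00 to 0.87 at an SD of change of 2, and from 2.00 to 1.73 at an SD of 4.

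**Step 3: what is left of a chance imbalance.** With equal SDs, a realised baseline difference D shifts the change-score difference by −(1 − rho)D in expectation. At rho 0.5, D = 1 point shifts it by 0.5 point. For scale, take a TNSS SD of 3. The standard error of D is 3 × √(2/32) = 0.75 with 32 per arm, and 3 × √(2/40) = 0.67 with 40. A one-standard-error imbalance then shifts the result by:
- 32 per arm: 0.52, 0.38 or 0.23 point at rho 0.3, 0.5 or 0.7
- 40 per arm: 0.47, 0.34 or 0.20 point

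**The case against.** The strongest reply is that nothing stated is wrong. With 1:1 randomisation a difference in mean change is unbiased over repeated trials, and its confidence limit already allows for chance baseline differences. That stands. A reader might infer from the 0.5-point shift that the planned analysis is biased or that its error rate is off. It is not: the shift is conditional on a realised 1-point imbalance. Nor is any stated power undermined, since the 80 were not derived from a power calculation.

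Second, the article is silent rather than explicit. It never calls the interval unadjusted, and a full protocol or analysis plan could specify ANCOVA. This also stands, so the point concerns the rule as written. Still, section 2.12 names tests for baseline, within-arm and adverse-event comparisons, but no estimator for the interval that decides the trial.

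Third, 64 is the number of completers, whereas section 2.12 analyses the full analysis set and carries last observations forward. The number analysed could approach 80, which is why both sizes are shown. The relative gain is essentially the same at either.

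Three further inferences go too far:
- **Undefined direction of the difference.** With higher TNSS worse and a rule that the upper limit lies below 2, only one coherent reading exists: phototherapy minus acupuncture in week 4 minus baseline, or its algebraic equivalent. Writing it out is a clarification only.
- **Wide baseline spread because there is no minimum TNSS.** Eligibility requires at least two of the four symptoms that the score sums, and the article gives no spread.
- **A loss of 18% to 54% as a property of this trial.** That range follows from an assumed rho of 0.3 to 0.7.

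**Conclusion.** The concern holds as a point of efficiency and of conditional bias, not of validity. As written, the deciding interval is the between-group difference in TNSS change with no baseline covariate. It is never more precise, in large samples, than the baseline-adjusted interval, and it keeps a fraction (1 − rho) of any chance imbalance when the SDs are equal.

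The size depends on a correlation that the article does not give. The gain is substantial at rho 0.3 to 0.5, moderate at 0.7 and small at 0.8 to 0.9. An advisable, low-cost improvement is the right weight; the plan is not invalid without it. Fixing the covariate in advance also rules out choosing between adjusted and unadjusted intervals after the baseline tests have been seen.

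**What to change.** In section 2.12, state that the primary estimate is the phototherapy minus acupuncture difference in TNSS change (week 4 minus baseline) from an ANCOVA with treatment and baseline TNSS, and that the upper limit of its one-sided 97.5% confidence interval is compared with +2. The change outcome in section 2.6.1 can stay: with baseline in the model, change and week-4 score give the same treatment estimate. This wording also makes the direction explicit.

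Replace the between-group significance tests at baseline with a descriptive table.

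The cost is a sentence or two in section 2.12. Baseline and week-4 TNSS are already collected, and neither the sample size nor the visit schedule changes. If an unpublished analysis plan already specifies this model, the article's wording need only be brought into line with it.

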We designed a pilot study to validate the clinical effects and safety of intranasal phototherapy for AR compared to those of acupuncture treatment, which is used as a usual care. Previous studies have demonstrated that acupuncture is effective at reducing symptoms of AR and improving QOL.^[29–31]^ International, multicenter clinical study showed that 4 weeks of acupuncture treatment could alleviate the symptoms of PAR more effectively than sham acupuncture and waitlist groups.^[16]^ This result suggested that acupuncture could be an effective and safe treatment for AR, and we chose 10 acupoints and set the treatment period based on this study. Acupuncture has been used to treat AR in Korean medicine. It can avoid side effects that may occur during drug use and lower the days of drug use in patients with AR.^[18,32]^ Additionally, treating patients with AR in routine care with additional acupuncture treatment has a long-lasting therapeutic effect.^[31]^ Recently, studies on acupuncture for allergic diseases including AR have been increasing in the United States, Germany, and China.^[33]^ It is suggested that acupuncture treatment has a beneficial effect on AR.^[16,34]^ In Korea, National Health Insurance (NHI) has covered Korean medicine services including acupuncture, moxibustion, cupping, and herbal preparations.^[35]^

The committee for New Health Technology Assessment (nHTA) in Korea assessed phototherapy for AR and made conclusions that further studies are needed on this topic for its clinical application since there is insufficient research result on safety and effectiveness of the technology on AR patients.^[36]^ We expect that the results of this study will provide evidence to verify the effects of intranasal phototherapy and basis for the evaluation of nHTA.

There has been increased interest in the development of Clinical Practice Guideline (CPG) in Korean medicine for establishment of its evidence and Korean medicine related health insurance policy, and AR is one of the target diseases. We expect that this study results will contribute to the development of treatment interventions in Korean medicine and establish evidence for “intranasal phototherapy”, which is included as a key question in the Allergic Rhinitis Korean Medicine Clinical Practice Guideline.

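### A significance test with about 40 patients per arm cannot support the stated aim to validate safety; the risk difference with its 95% CI should be the main safety comparison

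*Protocol article*

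**What the plan says.** The Discussion (section 3) states the purpose as follows: "We designed a pilot study to validate the clinical effects and safety of intranasal phototherapy for AR compared to those of acupuncture treatment". The Introduction uses the same verb. The Objective (section 2.1) and an earlier paragraph of the Discussion speak instead of assessing effects and safety.

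The Statistical analysis section (2.12) defines who is evaluated for safety: "All participants who received at least 1 session will undergo an adverse effect evaluation". It then names the between-group method: "To compare groups and the incidence frequency of adverse events related to the 2 groups, the Chi-Squared test or Fisher exact test will be used". Its significance threshold is given at the end of the section: "The level of significance will be set at 0.05 (2-tailed), except for the primary outcome". No other between-group safety comparison is stated. For the primary outcome, by contrast, the same section compares a confidence limit with a noninferiority margin of 2 points.

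The Sample size section (2.9) plans "40 in the intranasal phototherapy group and 40 in the acupuncture group" and says that "there will be no sample size calculation", because the aim is preliminary feasibility. The Safety section (2.11) lists events from nasal dryness and stinging to septum perforation, and has severity and causality recorded for each.

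**The concern.** To say that one treatment is about as safe as another is a claim about how large an excess of harm the data can rule out. A test of no difference does not answer that. When it is non-significant, it says only that the data did not exclude equality, and in a small trial that happens often even when the true difference is sizeable.

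Section 2.12 recognises this for efficacy, where the claim that phototherapy is not worse rests on a confidence limit. For safety, which the aim names beside efficacy, it states only a test. A reader would then have two incidences and a p-value to set against the word validate, and nothing that shows how much excess harm remains possible. What is at stake is the strength of the safety conclusion. The primary efficacy analysis is not affected.

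**Working it through.** **Inputs from the protocol article.** 80 patients, 1:1, 40 per arm (section 2.9). Two-sided 0.05, chi-squared or Fisher test (section 2.12). Safety set: everyone treated at least once (section 2.12), so up to 40 per arm.

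**Input that is assumed.** The article gives no AE rates. I assume 5%, 10% or 20% of acupuncture patients with at least one AE, and various higher rates with phototherapy.

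**The plan's own figure.** With 20% drop-out, 80 × (1 − 0.20) = 64 completers, which matches section 2.9: "A total of 64 patients are predicted to complete the study". That is 32 per arm, but it is not the safety denominator, since patients who leave after one session still count. I therefore use 40. No power for safety is stated, so there is none to reproduce.

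**Power.** Let a and b be the numbers of patients with an AE under phototherapy and acupuncture, with true rates p1 and p0. Exact power is the sum of Bin(a; 40, p1) × Bin(b; 40, p0) over all tables whose p-value is below 0.05. The chi-squared test is taken without continuity correction.

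| Acupuncture v phototherapy (assumed) | Fisher | Chi-squared |
|---|---|---|
| 5% v 10% | 4% | 15% |
| 5% v 20% | 41% | 57% |
| 10% v 20% | 16% | 25% |
| 10% v 30% | 53% | 63% |
| 20% v 40% | 41% | 50% |

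For 80% power against an acupuncture rate of 10%, the phototherapy rate would have to reach about 36% (chi-squared) or 38% (Fisher).

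**What a non-significant result leaves open.** Take 8/40 against 4/40, a difference of 0.20 − 0.10 = 0.10. Fisher's test gives p = 0.35. The Wilson 95% limits are 0.1050 to 0.3476 for 8/40 and 0.0396 to 0.2305 for 4/40. The Newcombe interval for the difference is:

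- lower: 0.10 − √[(0.20 − 0.1050)² + (0.2305 − 0.10)²] = 0.10 − 0.161 = −0.061
- upper: 0.10 + √[(0.3476 − 0.20)² + (0.10 − 0.0396)²] = 0.10 + 0.159 = 0.259

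That is about −6 to +26 percentage points. Other results that neither test would call significant reach further: 7 against 2 events has an upper limit of about +27 points, and 10 against 4 about +31. Identical counts of 4 and 4 still leave +14.

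**No events of one kind.** With 0 of 40, the exact two-sided 95% upper limit is 1 − 0.025^(1/40) = 0.088, or 8.8%. The one-sided 95% bound is 1 − 0.05^(1/40) = 0.072, or 7.2%.

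**The case against.** The strongest reply is that the harm lies in an inference the article does not make. A reader might infer that the sponsor will take a non-significant AE test as proof of comparable safety. No section says so, and section 2.12 can be read as a routine descriptive comparison. The Abstract and Introduction speak of preliminary evidence, the Abstract passes the safety question on to later trials, and section 2.9 calls the aim preliminary feasibility. This stands: the plan contains no faulty decision rule.

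A reader might also infer that a safety claim is headed for the Korean health technology assessment. The Discussion reports that the committee found too little research on safety and effectiveness, but what it hopes this trial will supply is evidence on effects and a basis for that evaluation. It does not offer a safety verdict.

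Three further points stand in part. AEs are one secondary outcome among several. Low power for AEs is common to all trials of this size, and the list in section 2.11 includes minor events, so a higher count of any AE is not in itself grave harm. An unseen SAP may add intervals.

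What remains is that the article itself fixes the comparison as a test and twice uses a verb which that test cannot support. A pilot without a power basis is the setting in which estimation serves better than testing, so its preliminary status argues for the change.

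**Conclusion.** The point holds as a mismatch between a stated aim and the stated method, and as an inexpensive improvement. A two-sided 0.05 test with about 40 per arm cannot validate safety against acupuncture. Under assumed acupuncture rates of 5% to 20%, a doubling of AE incidence would be missed at least about half the time with either test, and in most of the cases shown far more often. A tripling from 10% to 30% would be missed 37% (chi-squared) to 47% (Fisher) of the time. A non-significant result could be compatible with an excess of 26 points or more.

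The power figures rest on assumed rates; the intervals and the 8.8% limit depend only on the counts and on 40 per arm. The documents do not support the stronger statement that the sponsor plans to equate non-significance with safety.

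**What to change.** In section 2.12, make the main safety comparison the between-arm risk difference in participants with at least one AE, with its 95% CI, in all participants who received at least one session. Keep the chi-squared or Fisher p-value as descriptive only, and say that a non-significant value will not be read as comparable safety. For serious AEs and septum perforation, give the exact upper confidence limit per arm when none occurs.

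In sections 1 and 3, replace validate, as applied to safety, with assess preliminarily, in line with section 2.1 and the other Discussion paragraph.

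The AE data are already to be collected under section 2.11, so no patients, visits or measurements are added. The cost is one extra table and a more modest safety claim.
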